## Abstract

**Background:**

Available data assessing the efficacy of pulmonary rehabilitation for patients with chronic sarcoidosis are scant; for Germany, there are none at all.

**Objective:**

To gain information about the benefit of in-house pulmonary rehabilitation for patients with chronic sarcoidosis and for the health care system, we intend to collect data in a prospective multicenter “real-life” cohort trial.

**Methods:**

ProKaSaRe (Prospektive Katamnesestudie Sarkoidose in der pneumologischen Rehabilitation) [Prospective Catamnesis Study of Sarcoidosis in Pulmonary Rehabilitation] will assess a multimodal 3-week inpatient pulmonary rehabilitation program for adult patients with chronic sarcoidosis over a 1-year follow-up time. Defined specific clinical measurements and tests will be performed at the beginning and the end of the rehabilitation. In addition, questionnaires concerning health-related quality of life and the patients’ symptoms will be provided to all patients. Inclusion criteria will be referral to one of the 6 participating pulmonary rehabilitation clinics in Germany for sarcoidosis and age between 18 and 80 years. Patients will only be excluded for a lack of German language skills or the inability to understand and complete the study questionnaires. To rule out seasonal influences, the recruitment will take place over a period of 1 year. In total, at least 121 patients are planned to be included. A descriptive statistical analysis of the data will be performed, including multivariate analyses. The primary outcomes are specific health-related quality of life (St George’s Respiratory Questionnaire) and exercise capacity (6-minute walk test). The secondary outcomes are several routine lung function and laboratory parameters, dyspnea scores and blood gas analysis at rest and during exercise, changes in fatigue, psychological burden, and generic health-related quality of life (36-item Short Form Health Survey).

**Results:**

Funding was obtained on October 12, 2010; enrollment began on January 15, 2011 and was completed by January 14, 2012. Results are anticipated late summer 2015.

**Conclusions:**

Due to the large number of participants, we expect to obtain representative findings concerning the effectiveness of pulmonary rehabilitation for patients with sarcoidosis and to provide a dataset of assessed objective and subjective short- and long-term changes due to pulmonary rehabilitation. The results should form the basis for the planning of a randomized controlled trial.

**Trial Registration:**

German Clinical Trials Register: DRKS00000560; https://drks-neu.uniklinik-freiburg.de/ drks_web/navigate.do?navigationId=trial.HTML&TRIAL_ID=DRKS00000560 (Archived by WebCite® at http://www.webcitation.org/6dKb5X87R)

## Introduction

Sarcoidosis is a granulomatous systemic disease of still unknown etiology [1] that seemingly is caused by a combination of genetic and environmental factors [2]. The lungs and thoracic lymph nodes are impaired in approximately 90% of patients [3,4]. Because of the systemic nature of the disease, any organ (eg, eyes, heart, skin, kidneys, liver, and the central nervous system) can be affected [5]. Due to its various manifestations, sarcoidosis shows very heterogeneous clinical pictures [6-8].

The incidence and prevalence of sarcoidosis have not been precisely compiled for Germany. Estimates using data from the Bonn Sarcoidosis collective give a prevalence of approximately 44 per 100,000 inhabitants [9]. Sarcoidosis may occur at any age, although the age distribution peaks between 20 and 40 years; women are more affected than men [9]. Therapeutic strategies aim to reduce the progressing sarcoidosis symptoms. Spontaneous remissions occur in a high percentage of cases. Nevertheless, more than 20% of sarcoidosis patients will develop a chronic or recurrent form of the disease; up to 10% suffer serious complications such as lung fibrosis or cardiac symptoms. Unfortunately, up to 5% of all cases end fatally [9].

Depending on the affected organs, sarcoidosis may cause functional limitations and reduce quality of life. It is mostly accompanied by a pronounced fatigue [9-11] and myasthenia [12]. Systemic corticosteroids remain the treatment of choice when organ function is threatened or progressively impaired [13,14]. The muscle atrophy in sarcoidosis patients is the main reason why, in addition to medication, a rehabilitation program with particular emphasis on training [15] in a multidisciplinary treatment and management setting is strongly recommended for sarcoidosis patients [11,16-19]. In contrast to rehabilitation for patients with chronic obstructive pulmonary disease (COPD), the available data assessing the efficacy of pulmonary rehabilitation for patients with sarcoidosis are sparse; for Germany, there are no current data available at all [19-21]. Therefore, we intend to close this gap by collecting data in a prospective multicenter study, which should act as a pilot for the planning of a randomized controlled trial (RCT).

Rehabilitation in Germany is a statutorily regulated part of the health care system and is only approved when social participation and inclusion, daily life, and the professional activities of the patient are restricted by illness. Access to inpatient rehabilitation is only possible following a thorough investigation by physicians specializing in social medicine. Proof that all outpatient treatment options have been exhausted must also be provided.

ProKaSaRe (Prospektive Katamnesestudie Sarkoidose in der pneumologischen Rehabilitation) [Prospective Catamnesis Study of Sarcoidosis in Pulmonary Rehabilitation] is a “real-life” cohort trial and a prospective multicentric follow-up (catamnesis) study of sarcoidosis in pneumological rehabilitation. It is designed to assess the impact of a multimodal 3-week inpatient pulmonary rehabilitation on symptoms, exercise capacity, and health-related quality of life (HRQL) for adult patients with chronic sarcoidosis. ProKaSaRe has a 1-year follow-up time.

We intend to rule out seasonal influences by including patients over a recruitment phase of 12 months. By assessing changes over a long period in this cohort of chronic sarcoidosis patients, so far the largest worldwide, we hope to gain reliable insights into and sound evidence of objective and/or subjective short- and long-term health changes caused by pulmonary rehabilitation. The most important questions that should be answered with the ProKaSaRe study are:

What are the characteristics of patients treated in inpatient pulmonary rehabilitation?What are the short- and the long-term findings in view of symptoms, exercise capacity, and HRQL?Will the HRQL change after the patients are discharged and how will the HRQL develop in the 12 months following rehabilitation?

The aim of the ProKaSaRe study is to create a solid basis of empirical real-life data on the effectiveness of pulmonary rehabilitation for patients with chronic sarcoidosis, including clinical parameters, exercise capacity, quality of life, and psychological burden via a prospective, multicentric, real-life observational study.

## Methods

### Design

ProKaSaRe is a prospective, multicentric observational study. All participants will be observed undergoing the usual structured, multidisciplinary rehabilitation program (Figure 1), which routinely includes a diagnostic assessment consisting of lung function measurements, a 6-minute walk test (6MWT) and various laboratory tests (described subsequently). As part of the study, patients with chronic sarcoidosis will be asked to answer several questionnaires at the beginning and at the end of the usual pulmonary rehabilitation program, as well as after 3, 6, and 12 months.

Ethical approval was granted by the Ethical Committee of the Hannover Medical School, Hannover, Germany (Nr 877).

**Figure 1 figure1:**
[figure not shown]
Checkpoints for the different tests, measurements, and distribution of the questionnaire.

### Selection of Study Centers and Participants

Rehabilitation clinics specializing in pulmonary rehabilitation of sarcoidosis patients that have already showed interest during a planning conference initiated by the Bad Reichenhall clinic, Bad Reichenhall, Germany, will be formally invited to participate in the trial. All centers have proven sarcoidosis expertise and the selection will be made so that a variety of differing organizational structures, including private clinics and clinics under the auspices of the German statutory pension insurance scheme will be represented.

Based on the referral rate of previous years, we estimate that the participation of 6 pulmonary rehabilitation–specialized centers will be necessary to recruit a sufficient number of patients in 12 months to perform meaningful statistical data analysis.

To be eligible for inclusion in the ProKaSaRe study, patients must be referred for sarcoidosis to one of the 6 participating study centers for inpatient pulmonary rehabilitation by their physicians or by the hospital doctors following acute inpatient hospital treatment. If the leading rehabilitation diagnosis of sarcoidosis is confirmed by a pneumologist expert in sarcoidosis on admission to the rehabilitation program, every patient who is younger than 80 years and aged at least 18 years will be invited to participate in the trial. On receipt of written consent, the patients will be consecutively recruited to and enrolled in the study regardless of their type of health insurance to assess a representative study population.

Patients will only be excluded for poor German language skills, the inability to understand and complete the study questionnaires (due to lack of linguistic proficiency), or if no written consent can be obtained.

### Data Collection and Compilation

Data will be collected at 5 time points: T_0_-T_4_. Defined specific medical measurements and tests will be undertaken at the beginning and the end of the pulmonary rehabilitation program and a questionnaire concerning symptoms and HRQL will be provided at different points in time during the inpatient program and the follow-up period of 12 months (Table 1). Clinical data, sociodemographic data, medication and comorbidities, generic and illness-specific quality of life questionnaires and validated questionnaires documenting anxiety and depression, fatigue, and dyspnea will be monitored on admission at the start (T_0_) and at discharge from the rehabilitation program (T_1_) [22].

At T_0_, the core data will be compiled comprising sociomedical status, age, sex, body mass index (BMI), severity of sarcoidosis, and organ involvement and damage. Previous treatment will also be assessed.

The following clinical findings will be recorded by the doctors at the start (T_0_) and end (T_1_) of the rehabilitation program at each clinic using medical survey forms: lung function, gas exchange, physical fitness, and laboratory parameters. This includes the following measurements:

BMI [23]Lung function values: vital capacity (VC), residual volume (RV), total lung capacity (TLC), forced expiratory volume in 1 second (FEV_1_), specific airway resistance (sRaw), mouth occlusion pressure 0.1 seconds after onset of inspiration (P0.1), and maximal inspiratory mouth pressure (Pimax), and Tiffeneau-Index (the FEV_1_/VC ratio) [24]Gas exchange: blood gas analysis at rest and during exercise (25/50 Watt), transfer factor of the lung for carbon monoxide (Tlco) in a single breath (Tlco SB) and per alveolar volume (Tlco/Va)Physical fitness: 6MWT distance [25]Laboratory parameters: angiotensin-converting enzyme (ACE) and C-reactive protein (CRP)

The psychological burden will be also documented at T_0_ using the Hospital Anxiety and Depression Scale (HADS-D) [26] and quality of life by the 36-item Short Form Health Survey (SF-36) and the St George’s Respiratory Questionnaire (SGRQ) [27]. The fatigue symptoms, which are often predominant in sarcoidosis, will be assessed by the Fatigue Assessment Scale (FAS) [28,29] and dyspnea will be measured using the Modified Medical Research Council Dyspnea Scale (mMRC)[30-32]. At 3, 6, and 12 months (T2, T3, and T4) after the rehabilitation program, the FAS, HADS-D, mMRC [30], SF-36, and SGRQ questionnaires will be completed again by the patients. Although the questionnaires at T_0_ and T_1_ will be submitted on site, the ones at T_2_ to T_4_ will be sent by post. The patients will be instructed to complete all questionnaires independently.

In addition, the patients’ views of the components of the individual rehabilitation programs and their perceived importance will be assessed at discharge (T_1_). Moreover, an evaluation of the program from the patients’ perspective will be included in the final questionnaire at T_4._

During the whole study, response shift will be assessed by a questionnaire comprising 5 questions illustrating the prospective hopes of the patient and the retrospective specific burden of disease on the patient.

Data collection by post at 3, 6, and 12 months after discharge from the clinics will proceed by means of standardized letters with enclosed questionnaires and stamped return envelopes. The completed questionnaires will be returned to the clinic at which the rehabilitation program was carried out. Nonresponding patients will be reminded to answer the questionnaire by an additional letter after 2 weeks. Further details and the distribution times of the questionnaires and the documentation of their components are shown in Figure 1 and Table 1.

**Table 1 table1:** Components of the questionnaires given at the beginning of rehabilitation (T_0_), at the end of rehabilitation (T_1_), and at 3, 6, and 12 months after the end of rehabilitation (T_2_, T_3_, and T_4_).

Component	Content
1. Core data	Age, sex
2. Diagnoses	How they were secured or their positive proof
3. Organ involvement and general symptoms	
4. Lung function tests	VC, RV, TLC, FEV_1_, sRaw, Tiffeneau-Index (each before/after bronchospasmolysis), P0.1, and Pimax (T_0_, T_1_)
5. Gas exchange	Resting and exercise blood gas analysis (25/50 Watt), Tlco SB, Tlco/VA, (T_0_, T_1_)
6. 6MWT	6-minute walk test distance
7. mMRC	The Modified Medical Research Council Dyspnea Scale
8. Laboratory parameters	ACE, CRP
9. Health-related quality of life	SGRQ and SF-36
10. Psychological burden	HADS and FAS
11. Sociomedical status	Standardized questionnaire (patients’ self-development)
12. Sociomedical patient questionnaire	Standardized questionnaire (patients’ self-development)
13. Evaluation of rehabilitation program	Evaluation of the rehabilitation program from the perspective of the patient
14. Components of rehabilitation program	Components of the individual rehabilitation program and its (patient) attributed value
15. Response shift	Prospective hopes and the retrospective specific burden of disease

All questionnaires and documents will be anonymized at the 6 participating rehabilitation centers and sent to the Hannover Medical School in Hannover, Germany, for digitalization via independent double data entry by 2 individuals who are not involved in patient care.

### Sample Size Calculation and Statistics

Sample size calculation was carried out separately for both primary endpoints. Because both endpoints are equally important, the type I error was adjusted by Bonferroni multiplicity adjustment.

The minimal clinical difference for the health-related SGRQ corresponds to a change of 4 points in the score for patients with COPD. This value was also used in the planning of this study because no sarcoidosis-specific reference values were available. According to Jones [33], a 4-point difference between baseline values and follow-up data would indicate clinically relevant (long-term) effects. From the 95% confidence interval he observed in 97 patients, we estimated a standard deviation of 12.1. Assuming a 2-sided type I error of 2.5% and a power of 90%, the overall sample size required based on a paired *t* test would be 115 patients.

One estimated minimal clinical difference for the 6MWT distance corresponds to 26 m [34]. In absence of sarcoidosis-specific references, we suggest according to Marcon [35], a 6MWT distance of approximately 600 m (SD 80). Assuming a 2-sided type I error of 2.5% and a power of 90%, the overall sample size on the basis of a paired *t* test is 121. Thus, at least 121 patients are needed to test for both primary endpoints. To avoid a systematic “center bias,” each center should recruit at least 30 patients. Sample size calculations were performed using nQuery Advisor7.0.

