### Data Management and Statistical Analysis Procedures

Data management will be carried out by the Centre for Public Healthcare and statistical analysis by the Institute for Biostatistics at the Hannover Medical School.

The questionnaires will be anonymized using a clinic identifier and a consecutive patient number and will be digitized in duplicate at the Hannover Medical School and entered in Microsoft Access. The database tables will then be virtually superposed to identify differences between entries. When discrepancies are found, the data entry will be compared with that of the original questionnaire and corrected so that an accurate master dataset used for the descriptive analysis and the calculation of effect sizes will emerge.

The main analyses will be performed on the total study population. Missing values will be reported and not replaced initially. Changes in both primary endpoints between T_0_ and T_1_ will be evaluated with a paired *t* test and a 2-sided type I error of 2.5%.

Because ProKaSaRe is an exploratory study, for all analyses except for the primary analysis, *P* values will be assessed descriptively and considered to be of importance for *P*<.05. Therefore, no adjustment for multiplicity will be performed. Descriptive evaluation of clinical characteristics will be conducted. Changes from baseline for continuous data will be compared by paired *t* tests and given with 95% confidence intervals for the mean difference. Categorical parameters will be compared for T_1_ to T_4_ by chi-square test. Duration of sick leave and results of the sociomedical status documented by the physician (T_0_, T_1_) and by the patient (T_2_, T_3_, T_4_), the evaluation of rehabilitation from the patients´ perspective (T_1_) and patient-attributed value to the components of the individual rehabilitation program will be presented exploratively. For the questionnaires, a covariate analysis will be run using participating centers and baseline values as independent variables and the change from T_1_ and T_2_ to T_0_ as dependent variables. Further multivariate analyses are planned.

All statistical analyses will be conducted using the SAS 9.3 software (SAS Institute Inc, Cary, NC, USA) to show the impact of the rehabilitation program on the patients’ lives.

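### The 6MWT calculation that sets N = 121 enters an SD of walking distance where the paired t test needs the SD of the change, so its 90% power is not supported

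*Protocol article*

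**What the plan says.** All figures are in the protocol article. Under Sample Size Calculation and Statistics, each primary endpoint is sized separately and "the type I error was adjusted by Bonferroni multiplicity adjustment", which gives 2.5% two-sided for each.

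For the 6MWT, the effect is set by "One estimated minimal clinical difference for the 6MWT distance corresponds to 26 m" and the variability by "a 6MWT distance of approximately 600 m (SD 80". Both go into a paired t test at two-sided 2.5% and 90% power, with the result 121. For the SGRQ, the effect is 4 points, the SD is 12.1 and the result is 115. The larger figure is carried forward: "Thus, at least 121 patients are needed to test for both primary endpoints". The same section asks each center to recruit at least 30 patients, and Selection of Study Centers and Participants names 6 centers.

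The primary test is fixed under Data Management and Statistical Analysis Procedures: "Changes in both primary endpoints between T_0_ and T_1_ will be evaluated with a paired" t test at two-sided 2.5%.

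The article gives neither an SD of the T0-T1 change in 6MWT distance nor a correlation between the two measurements.

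**The concern.** The 80 m is attached to a distance of about 600 m. It describes how far people differ from one another, not how much one person changes over three weeks. A paired t test removes stable differences between people, so its power depends on the SD of the change alone. That SD can be larger or smaller than 80 m, depending on how closely the two walks of one patient agree.

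This is the line that fixes the trial's minimum size. If its SD is the wrong kind of SD, then both the 121 and the 90% power attached to it lack a basis for the test that will be run. The same figures could also be carried into the randomized trial that the article says should be planned from these results.

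**Working it through.** **Inputs.** Difference 26 m, SD 80 m, two-sided alpha 0.025 and power 0.90, all from Sample Size Calculation and Statistics. The paired t test on T0-T1 changes is from Data Management and Statistical Analysis Procedures.

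**Step 1: reproduce the stated figure.** The exact power of a paired t test uses the noncentral t distribution with n − 1 degrees of freedom and noncentrality (26 / SDdiff) × √n. With SDdiff = 80 and n = 121, the noncentrality is (26 / 80) × 11 = 3.575, the critical value is 2.270 and the power is 0.9025. The smallest n that reaches 0.90 is 121, exactly as stated. The normal approximation gives 118. Alpha 0.05 gives 102, and a two-sample layout gives 236 per arm. The plan's figure therefore matches 80 m entered directly as the SD of the paired difference.

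**Step 2: what that implies.** If the SD of distance is 80 m at both T0 and T1, then SDdiff = 80 × √(2(1 − rho)). Setting SDdiff = 80 gives 2(1 − rho) = 1, so rho = 0.5.

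**Step 3: how much depends on it.** The article gives no rho, so the values below are assumptions shown as a range. The last column uses 6 × 30 = 180 patients.

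| Assumed rho | SDdiff (m) | N for 90% power | Power at 121 | Power at 180 |
|---|---|---|---|---|
| 0.3 | 94.7 | 168 | 77% | 92% |
| 0.4 | 87.6 | 144 | 84% | 96% |
| 0.5 | 80.0 | 121 | 90% | 98% |
| 0.6 | 71.6 | 97 | 96% | >99% |
| 0.7 | 62.0 | 74 | 99% | >99.9% |
| 0.8 | 50.6 | 50 | >99.9% | about 100% |
| 0.9 | 35.8 | 27 | about 100% | about 100% |

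**Step 4: the other primary endpoint.** For the SGRQ, a difference of 4 with SD 12.1 gives an exact N of 117, against 115 as stated. An SD of 12.0 gives 115 and 12.05 gives 116, so the gap may be no more than rounding of the SD. Once rho is a little above 0.5, the 6MWT requirement falls below 115 to 117 and the SGRQ sets the minimum.

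**The case against.** The best defense is that the arithmetic is right and the practical effect is small. Much of this stands. The 121 is correct for the inputs given. The cited source cannot be seen, and the authors may have adopted 80 m deliberately as a cautious SD of the change. If so, the article needs to say so, because its wording ties the 80 m to a distance.

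A reader might infer several stronger things that the documents do not support:

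- **That the 90% is shown to be false, or the study underpowered.** No rho is given, and at rho 0.5 the power is 90%. The 77% and 84% hold only at the bare minimum of 121. At 180 they become 92% and 96%, although 30 per center is a target and not a guarantee.
- **That 74, 50 or 27 patients would have been enough for the trial.** Both primary endpoints must be served, so with a high rho the SGRQ holds the minimum at 115 to 117, only 4 to 6 below 121.
- **That the SD makes significance below 26 m a fault of the test.** With SDdiff = 80, the smallest significant mean change at 121 is already 2.270 × 80 / 11 = 16.5 m. A smaller SD lowers this through better precision. The test remains valid at 2.5% whatever rho is.
- **That the two endpoints are demonstrably sized on different bases.** For the SGRQ the article says only "From the 95% confidence interval he observed in 97 patients, we estimated a standard deviation of 12.1". It does not say what that interval was for.

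Enrollment also ended in January 2012, so no recruitment decision now hangs on this.

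**Conclusion.** The point holds as a mismatch between a stated input and a stated test. An SD given for walking distance is used as the SD of the T0-T1 change, and the 90% power is therefore unsupported for the planned 6MWT analysis. Over assumed correlations from 0.3 to 0.9, the N needed for this endpoint runs from 168 to 27, and power at 121 runs from 77% to about 100%.

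The direction of the error is open. The effect on the trial's minimum is small if rho is above about 0.5. If rho is lower, the shortfall at 121 is real but is made good at rho 0.3 and 0.4 if 180 patients are reached.

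The conclusion rests on reading 80 m as the article words it, on equal SDs at T0 and T1, and on values of rho that are assumed.

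**What to change.** In Sample Size Calculation and Statistics:

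1. Replace SD 80 with a justified SD of the T0-T1 change in 6MWT distance. Alternatively, keep 80 m as the SD of distance and add a stated rho with a range. If 80 m was meant as the SD of the change, say so and give the reason.
2. Restate the 6MWT sample size and power on that basis, at 121 and at the 180 implied by the center target.
3. State that if rho exceeds about 0.5, the SGRQ sets the minimum (115 as stated, 117 by exact calculation with SD 12.1).

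Optionally, read the 6MWT change against the plan's own 26 m through its confidence interval. The analysis section already plans 95% intervals for mean changes, so only the comparison is new.

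The cost is one recalculation and one rewritten paragraph. Because enrollment has closed, it calls for no additional patients, and the planned test does not change.
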